### Trial design and randomization

This study will utilize a single-blinded, randomized 2 × 2 factorial design (see Fig. 1). Block randomization will be used to allocate participants to one of four arms with random block sizes, stratified by participant sex. The randomization allocation table will be implemented using the REDCap randomization framework using an allocation ratio of 1:1:1:1 and will occur directly before treatment assignment. The randomization process will be overseen by an independent statistician, who is not involved with study procedures, including participant recruitment, intervention assignment, or any other forms of participant contact. Randomization results will only be directed to the study coordinator, who will assign participants to the intervention groups. All other study staff including the trial investigators, and data analyst will be blinded to treatment assignment. Care providers will not be informed of treatment assignment, and participation in the study will not affect clinical care. Participants may therefore engage in any other intervention or treatment (e.g., counseling, physical therapy). In the unlikely event of an adverse event, unmasking would be permissible.

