### Primary efficacy outcomes

*Hypothesis 1 (acute outcomes): Adolescents receiving pre-operative CBT will have a faster rate of recovery of pain severity and interference during the 14 days following hospital discharge, compared to adolescents who receive pre-operative education.* The acute outcomes will be assessed before any post-operative intervention has taken place. Therefore, arms 1 and 3 will be combined into the control group (pre-operative education); arms 2 and 4 will be combined into the intervention group (receiving pre-operative CBT intervention) for this analysis (see Table 4). We will apply nonlinear mixed effects models with an exponential decay functional form, to evaluate individual rate of recovery in daily pain severity and interference, or how quickly the process decays/improves from the initial value to the asymptote. Rate parameters will be estimated using restricted maximum likelihood (REML) approach and compared using multivariate Wald test. As a further primary analysis, we will treat daily pain severity and interference as repeated measures using generalized estimating equations (GEE) to account for clustering within participants.

**Table 4 Tab4:** Treatment arms

Group	Pre-operative phase	Post-operative phase
1	ED	ED
2	CBT	ED
3	ED	CBT
4	CBT	CBT

*ED* online education, *CBT* Cognitive Behavioral Therapy Intervention

*Hypothesis 2 (chronic outcomes): Adolescents receiving post-operative CBT alone will have lower pain severity and interference, compared to adolescents receiving education control at 3 months.* We will consider the education control arm (arm 1) as the control group and post-operative CBT alone arm (arm 3) as the intervention group. Covariates adjusted linear regression models will examine group differences in average pain severity and interference, as continuous outcomes, at 3 month follow-up.

*Hypothesis 3 (chronic outcomes): Adolescents receiving both phases of peri-operative CBT will have lower pain severity and interference compared to adolescents receiving single phase (pre- or post-surgery) intervention or education control alone at 3 months.* We will apply linear regression models to examine differences in average pain severity and interference between individual study arms, treated as a 4-level categorical predictor variable.

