### Sample size and power calculations

Power calculations on primary pain outcomes are based on data available from our preliminary peri-operative studies [4, 7, 31] and from prior peri-operative intervention studies [16–18]. Power analyses for primary acute outcomes were based on rate of recovery using an exponential decay model. Based on pilot data, we assume log(rate) = − 1.21 (SE = 0.38) in the intervention arm, which translates into a half-life (days taken to achieve 50% reduction in BPI outcome from time 0) of 4.13 days. Using a conservative estimate of 35% increased half-life of recovery in the control arm, 31 subjects per arm would provide 90% power; N = 24/arm for 80% power.

For the second acute parameter of interest, power calculations were performed using GEE model on time-averaged difference (TAD) using individual daily repeated measures of BPI scores. In order to detect a group difference of 1.2 with standard deviation 2.0, we need to enroll 199 participants into each of the two comparison groups (total sample of 398; assuming 1:1 allocation of subjects into pre-operative education vs. intervention, within-subject observations follow AR(1) correlation pattern with a correlation coefficient of 0.7, and a missing completely at random rate of 5% each day).

For the primary chronic pain outcomes, to detect a group difference of 1.0 with standard deviation 1.8, 35 subjects are needed per arm for 80% power based on two-sample t test.

The target complete sample is 400 adolescent/parent dyads. Conservatively accounting for 20% attrition, we plan to enroll 500 adolescents but will adjust this if completion rates are > 80%.

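### The 35 per arm stated for the primary chronic pain outcomes does not follow from its own inputs: a 1:1 t test at two-sided 5% needs 52, although the planned size comfortably exceeds that

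*Protocol article*

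**What the plan says.** For the primary chronic pain outcomes, the section on sample size and power calculations gives one power statement, namely "to detect a group difference of 1.0 with standard deviation 1.8, 35 subjects are needed per arm for 80% power based on two-sample t test". Difference, SD, power, test and number per arm are all fixed there. The significance level and the sidedness of the test are not stated anywhere in the article.

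The comparisons that this statement has to serve are under the primary efficacy outcomes. For Hypothesis 2, "We will consider the education control arm (arm 1) as the control group and post-operative CBT alone arm (arm 3) as the intervention group". For Hypothesis 3, differences are examined "between individual study arms, treated as a 4-level categorical predictor variable". Participants are randomised "using an allocation ratio of 1:1:1:1", so each comparison of two arms is 1:1.

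The overall size is set separately. The target is 400 complete dyads, and "Conservatively accounting for 20% attrition, we plan to enroll 500 adolescents".

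**The concern.** A difference of 1.0 with SD 1.8 is a standardised effect of about 0.56. A two-sample t test at the usual 5% two-sided level needs about 50 per arm for 80% power at that effect size, so 35 looks too small.

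Two of the three primary hypotheses concern the chronic outcomes, and this sentence is their only published power justification. A reader who takes it at face value would believe that 35 per arm leaves a 20% chance of missing a true 1.0-point difference. At two-sided 5% that chance is about 37%.

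**Working it through.** **Inputs**
- Difference 1.0, SD 1.8, power 80%, two-sample t test: sample size and power calculations.
- Allocation 1:1 between any two arms: trial design and randomization, and Hypotheses 2 and 3.
- Significance level: not stated. Assumed two-sided 0.05, with other levels shown below.
- Completers per arm: 500 × 0.80 = 400, and 400 / 4 = 100.

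**Step 1: try to reproduce 35.** The standardised effect is d = 1.0 / 1.8 = 0.556. By the normal approximation,

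n per arm = 2 × (1.960 + 0.842)² × 1.8² / 1.0² = 2 × 7.849 × 3.24 = 50.9, so 51.

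The noncentral t calculation gives 51.8, so 52 per arm. Power is 80.1% at 52 and 79.3% at 51. The stated 35 is not reproduced.

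**Step 2: power at 35 per arm.** The noncentrality is 0.556 × √(35/2) = 2.324. The normal approximation gives Φ(2.324 − 1.960) = 64.2%. The t test gives 63.0%.

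**Step 3: vary the unstated significance level** (t test, 1:1).

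| Level | n per arm for 80% power | Power at 35 per arm |
|---|---|---|
| two-sided 0.025 | 63 | 51.6% |
| two-sided 0.05 | 52 | 63.0% |
| one-sided 0.05 (or two-sided 0.10) | 41 | 74.4% |
| two-sided 0.20 | 30 | 84.8% |

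Exactly 80% power at 35 per arm would need a two-sided level of about 0.14, which is not a conventional choice.

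**Step 4: find what would return 35** (two-sided 0.05).
- A difference of about 1.22 with SD 1.8.
- An SD of about 1.47 with difference 1.0.
- A 1:3 t test of one arm against the other three pooled: 34.4, so 35 in the single arm and 105 in the pooled group, with 80.7% power.
- A covariate-adjusted variance with a baseline–outcome correlation of about 0.57: 50.9 × (1 − 0.57²) = 50.9 × 0.675 = 34.3, so 35.
- A one-sample or paired test does not return 35; it needs 28.

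**Step 5: power at the planned size** (100 completers per arm, t test).

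| Level | Power for 1.0 | Difference detectable with 80% power |
|---|---|---|
| two-sided 0.05 | 97.4% | 0.72 |
| two-sided 0.025 | 95.2% | 0.79 |

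**The case against.** The strongest case on the other side has three parts.

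**Nothing in the design rests on 35.** The largest requirement in the same section is 199 per comparison group (398 in total) for the time-averaged acute outcome. That is what lines up with the target of 400. About 100 completers per arm is nearly twice 52. This stands, and it limits the point to a wrong stated figure.

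**The significance level is an assumption.** The figure of 52 depends on two-sided 5%, which the article does not state. This stands as a caveat, but it does not rescue the sentence: one-sided 5% still needs 41, and a multiplicity-adjusted level would need more than 52.

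**The error may not be in the 35.** The difference, the SD or the description of the test could be wrong instead. The two unstated set-ups that return 35 both echo features of the plan. Arm 4 is compared with arms 1, 2 and 3 in the exploratory analyses, and the regression models adjust for pre-surgery pain. The article gives neither as the basis of the calculation. It describes a plain t test with a number per arm and states no correlation, and a 1:3 comparison would not cover Hypothesis 2. This part bears on the fix, which should leave room for another source of the error.

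A reader might go further and infer that the trial is underpowered for chronic pain, or that the figure could lead to early stopping or a cut in enrolment. The article supports neither reading. Its provision for adjusting recruitment concerns the 500 to be enrolled if completion exceeds 80%, and the target of 400 completers stays as stated. No interim analyses are planned.

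**Conclusion.** The stated number is wrong for the test and inputs given. At two-sided 5% the requirement is 52 per arm, so 35 is about one third too low (17 / 52 = 33%), and power at 35 is about 63% where 80% is claimed. At one-sided 5% the figures are 41 and about 74%. The conclusion rests on 1:1 comparisons of single arms, as Hypotheses 2 and 3 define them, and on a conventional significance level. It does not depend on which conventional level is chosen.

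The consequence is confined to reporting. If retention is as planned, power for a 1.0-point difference is about 97% at two-sided 5% and about 95% at two-sided 2.5%. The published justification for a primary outcome needs correcting, but design, enrolment and analysis are unaffected.

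**What to change.** Replace 35 with 52 per arm and state that the calculation uses a two-sided 5% level. If 35 came from a different difference, SD, significance level, comparison or covariate adjustment, state that basis and reword the sentence to match. A 1:3 basis would also need a separate statement for Hypothesis 2.

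In either case, add the figure that describes this trial: at 100 completers per arm and two-sided 5%, about 97% power for a difference of 1.0, or 80% power for about 0.72. If a stricter level applies, give the corresponding figures (about 95% and 0.79 at two-sided 2.5%).

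The cost is one or two sentences, with no change to the sample size or conduct.

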### Oversight and monitoring

Study monitoring to ensure proper consenting and assenting procedures, maintenance of IRB approval, intervention implementation, and security of databases will be conducted by Trial Innovation Centers (TICs) including the University of Utah DCC and Duke/Vanderbilt Clinical Coordinating Centers (CCCs). The DCC will work closely with research coordinators and principal investigators to oversee study data management. In addition, an independent Data and Safety Monitoring Board (DSMB) comprised of experts from pediatric psychology, behavioral interventions, and statistics will convene biannually in an open session followed by a closed session to review study progress, data, and participant safety. Authorship will be determined in accordance with the HEAL Initiative Publication Policy.

## Discussion

This study will address a critical gap in knowledge of perioperative interventions targeting psychosocial risk factors to prevent transition from acute to CPSP in adolescents undergoing spinal fusion surgery. Our trial will use an innovative factorial design to test two intervention phases, pre-operative and post-operative, in order to determine the optimal timing of intervention delivery. This study will build on prior research examining short-term efficacy of peri-operative psychosocial interventions to reduce acute pain intensity by testing improvement on clinically meaningful and longer-term post-surgical outcomes such as chronic pain interference and quality of life. In addition, our recruitment design across multiple pediatric spine centers allows for broad inclusion of youth undergoing spinal surgery at community and academic hospital sites in many different regions of the USA.

To engage wide participation in a peri-operative program, interventions must use flexible, accessible, low-cost delivery models. Research with family stakeholders indicates that teens and parents prefer technology-based delivery within the current system of peri-operative care [45]. To address these needs, we developed the CBT and education interventions to be flexibly delivered via a mobile application and website for deployment in the trial. If successful, following the trial, we will have the unique opportunity for widespread dissemination of the SurgeryPal^TM^ interventions to adolescents receiving care in pediatric spine centers across the country.

The USA currently faces two national health crises relevant to perioperative pain management: rising rates of chronic pain, and an epidemic of opioid addiction and overdose, both of which extend to adolescents [46–49]. Neurobiological and psychosocial changes occurring during adolescence increase vulnerability to both drug addiction [50] and chronic pain [51]. Pain problems and opioid use/misuse often begin in adolescence and place individuals at risk for lifelong problems [52, 53]. Thus, prevention strategies addressing these health crises must address risk during this vulnerable developmental period. Major musculoskeletal surgeries, such as spinal fusion, are frequently timed for the adolescent period, and are associated with high rates of chronic postsurgical pain. Moreover, opioids are the cornerstone for pain management after these surgeries, and opioid-naïve youth undergoing surgery are at elevated risk for developing persistent opioid use over the subsequent year [54]. Adolescents undergoing major surgeries urgently need effective therapies to reduce pain, in order to mitigate potential for chronic pain, and to reduce exposure to opioids.

By studying a model of prevention during two intervention phases, this trial will take a critical step in pain research by examining whether psychosocial interventions implemented before the inciting event (primary prevention) and/or during the recovery phase (secondary prevention) may prevent acute to chronic pain transition. In addition, this RCT is designed to explore mechanisms underlying treatment effect, which will advance understanding of the transition from acute to chronic pain.

## Trial status

Recruitment started December 2020. The current approved protocol is version 1.08 (Initial submission approval date: 07 April 2020; approved version at final journal submission: 28 April 2021). Recruitment is estimated to be complete by December 2023. Any protocol modifications will be updated on ClinicalTrials.gov and on the participants’ consent form.

## Data Availability

The study protocol has been reported in accordance with the Standard Protocol Items: Recommendations for Clinical Interventional Trials (SPIRIT) guidelines (Additional file 1). The data collection forms are available from the corresponding author on request. A database for underlying primary data for publications will be made publicly available on the NIH HEAL Initiative central data repository. The database will be de-identified in accordance with the definitions provided in the Health Insurance Portability and Accountability Act (HIPAA) and will be accompanied by a data dictionary that provides a concise definition of every data element included in the database. The policies for release of and access to this database are in accordance with the HEAL Data Sharing policy as determined by the NIH. Results of this trial will be published in international peer-reviewed journals by the study team.

## Abbreviations

BPI: Brief Pain Inventory
CPSP: Chronic postsurgical pain
